### Study objectives

This study aims to systematically characterize the 5-year natural history of pDoC through a prospective cohort design, thereby bridging the critical evidence gap stemming from the absence of large-scale, long-term follow-up investigations. The specific objectives are as follows:To determine the rates of consciousness recovery, all-cause mortality, and major cardiovascular events over a 5-year follow-up period in patients stratified by initial level of consciousness (VS, MCS−, and MCS+); primary comparisons will be conducted at the VS vs. MCS level, with MCS − vs. MCS + differentiation examined in prespecified subgroup analyses.To identify etiology, injury severity (GCS at admission), time from injury to enrollment, Coma Recovery Scale–Revised (CRS-R) subscale profiles, and neuroimaging indices as independent predictors of consciousness recovery and unfavorable outcomes.To develop and validate a multimodal prognostic prediction model integrating clinical, neuroimaging, and biomarker data.

The primary research question of this study is: among patients with prolonged disorders of consciousness (VS or MCS ≥ 28 days post-acute brain injury), does baseline consciousness level (VS vs. MCS) independently predict 5-year consciousness recovery trajectory, after adjustment for etiology, injury severity, and neuroimaging characteristics?

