### Variables

#### Primary and secondary outcome variables

The primary outcome variables of this study are as follows: (1) pDoC recovery, defined as emergence from MCS (eMCS), operationalized as achieving a CRS-R communication subscale score ≥2 (functional interactive communication) or a motor subscale score ≥6 (functional object use), confirmed on ≥2 standardized CRS-R assessments conducted ≥7 days apart and sustained for ≥4 consecutive weeks. This criterion applies uniformly to patients with a baseline diagnosis of VS or MCS. All recovery determinations will be adjudicated by the independent Endpoint Adjudication Committee; (2) all-cause mortality, defined as death from any cause at any point during the 5-year follow-up period (up to and including month 60). In the competing-risk analytical framework, all-cause mortality serves as the primary competing risk event for the consciousness recovery outcome. Patients who survive to the end of the 60-month follow-up without having achieved the consciousness recovery endpoint will be administratively right-censored at month 60; and (3) major cardiovascular events (MACE), encompassing myocardial infarction (defined in accordance with the Fourth Universal Definition of Myocardial Infarction, requiring elevated cardiac biomarkers in conjunction with clinical evidence of myocardial ischemia), hospitalization for heart failure (defined as inpatient admission requiring intravenous diuretics or inotropic support), and stroke (confirmed by neuroimaging [CT/MRI] with neurological deficits persisting for more than 24 h).

Secondary outcome variables include: (1) changes in functional status, assessed using the Glasgow Outcome Scale–Extended (GOS-E) and the Disability Rating Scale (DRS) (8, 9); (2) dynamic changes in biomarkers, including serum neurofilament light chain (NfL), glial fibrillary acidic protein (GFAP), S100 calcium-binding protein B (S100B), and other injury- and recovery-related biomarkers; (3) health-related quality of life, evaluated using the EQ-5D questionnaire, with caregiver proxy responses employed when direct patient assessment is not feasible; and (4) rehospitalization rate, documented by recording the frequency and causes of readmission, with particular attention to common complications such as infections, seizures, and respiratory events.

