### Follow-up procedures

Follow-up assessments will employ a hybrid surveillance strategy combining in-person evaluations with remote monitoring. Core neurobehavioral and functional assessments (CRS-R, GOS-E, DRS, EQ-5D, SF-36, FIM, HADS, and Zarit Caregiver Burden Interview) will be conducted at bedside by certified assessors at baseline and at 3, 6, 12, 24, 36, 48, and 60 months (8 assessment timepoints in total, comprising 7 in-person follow-up visits). The Chinese validated CRS-R (7) will be used throughout. Assessors must complete standardized training—covering scoring, ≥10 supervised assessments, and ICC ≥ 0.85 reliability—before independent use. The same assessor will evaluate each participant at all timepoints when feasible; if replaced, inter-rater reliability will be verified against the prior assessor’s last two evaluations. Total and subscale scores will be recorded at each visit. eMCS is defined by subscale-specific behavioral thresholds (per Primary Outcome Variables), not a total score of 23/23, which reflects full neurological recovery rather than functional communication or object use. Neuroimaging investigations (MRI/DTI/fMRI) and serum biomarkers (NfL, S100B, GFAP, and other injury-related biomarkers) will be performed at baseline and at 6, 12, 24, 36, 48 and 60 months. Following the 6-month visit, remote follow-ups will be conducted by telephone interview supplemented by caregiver-reported outcomes at 3-month intervals between scheduled in-person visits, primarily capturing vital status, rehospitalization events, and major adverse events. Remote follow-ups will be administered by uniformly trained research coordinators using standardized scripts, with video calls employed as an adjunct to confirm the patient’s general condition. In-person outpatient visits will be conducted by neurologists and rehabilitation therapists.

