## Statistical analysis methods

### General principles and descriptive statistics

All statistical analyses will employ two-sided tests with a significance threshold of α = 0.05, and results will be reported with 95% confidence intervals. Bonferroni correction or false discovery rate (FDR) adjustment will be applied to control Type I error inflation in the context of multiple comparisons. Multivariable regression models will be constructed within the competing-risk framework to identify independent prognostic predictors of consciousness recovery, as detailed in the Primary Analysis subsection below. Separately, a dedicated multimodal prognostic prediction model will be developed and validated using a three-stage hierarchically nested approach incorporating LASSO-based variable selection and bootstrap internal validation (1,000 resampling iterations); the C-index will serve as the primary discrimination metric. The full construction procedure for this prediction model is described in the dedicated subsection below.

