### Secondary analyses and longitudinal data analysis

Secondary outcomes will be analyzed using methods appropriate to each variable type: changes in functional status scores will be modeled using linear mixed-effects models or generalized estimating equations (GEE) to account for within-individual correlations in repeated-measures data; dynamic biomarker changes will be assessed using repeated-measures analysis of variance (ANOVA); quality-of-life scores will be analyzed using generalized linear models; and rehospitalization rates will be modeled using negative binomial regression. All models will account for time effects and between-individual variability.

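### EQ-5D, scheduled at eight timepoints per patient, is assigned an ordinary generalized linear model, while functional scores on the same schedule get mixed models or GEE; the quality-of-life clause should name a model class that handles within-patient correlation

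*Protocol article*

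**What the plan says.** All from the protocol article.

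- **Outcome.** Primary and secondary outcome variables lists, as a secondary outcome, "health-related quality of life, evaluated using the EQ-5D questionnaire, with caregiver proxy responses employed when direct patient assessment is not feasible".
- **Schedule.** Follow-up procedures puts EQ-5D in the same bedside battery as CRS-R, GOS-E and DRS, "at baseline and at 3, 6, 12, 24, 36, 48, and 60 months (8 assessment timepoints in total, comprising 7 in-person follow-up visits". Table 1 marks EQ-5D and the functional scales at the same eight columns.
- **Model for functional scores.** Secondary analyses and longitudinal data analysis gives them "linear mixed-effects models or generalized estimating equations (GEE) to account for within-individual correlations in repeated-measures data".
- **Model for quality of life.** Later in the same sentence: "quality-of-life scores will be analyzed using generalized linear models". No random effect, working correlation or clustered variance is attached.
- **Closing commitment.** The paragraph ends: "All models will account for time effects and between-individual variability".
- **Testing convention.** General principles and descriptive statistics sets "two-sided tests with a significance threshold of α = 0.05" for all analyses.

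**The concern.** Two sets of scores with the same repeated-measures structure receive different model classes in one sentence, and only one of them is given a way to handle correlation. Because mixed models and GEE are named a few words earlier, an analyst could reasonably read the plainer label for EQ-5D as a deliberate choice and fit it literally.

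An ordinary generalized linear model assumes independent observations. It can carry visit as a covariate and so meet the part of the closing commitment about time. It has no term for differences between patients that persist across visits. The named method and the closing commitment therefore do not sit together.

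At stake is the validity of confidence intervals and p-values for one named secondary outcome. Any comparison of patients with each other (by baseline state, etiology or age, for example) would look more certain than it is. Any comparison of a patient with himself or herself over time would look less certain than it is.

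**Working it through.** **Plan's own figure.** The article gives no precision, power or error figure for the quality-of-life analysis, so there is none to reproduce. The calculation below shows what would follow if the model were fitted as named to all scores pooled.

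**Inputs**
- Scheduled scores per patient: at most 8 (Follow-up procedures, Table 1). A range of 4 to 8 is assumed, since deaths and losses will shorten many series.
- Two-sided alpha of 0.05 (General principles and descriptive statistics), critical value 1.96.
- Within-patient correlation of EQ-5D, ρ: not in the document. Assumed 0.3 to 0.7, equal between all visits.

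**1. Between-patient contrast (group main effect)**

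With k scores per patient, the true variance of the contrast exceeds the independence variance by the design effect DE = 1 + (k − 1)ρ. The naive standard error is 1/√DE of the true one, and the actual type I error is 2[1 − Φ(1.96/√DE)].

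| k | ρ | DE | naive SE / true SE | actual type I error |
|---|---|---|---|---|
| 4 | 0.3 | 1 + 3 × 0.3 = 1.9 | 0.725 | 15.5% |
| 4 | 0.5 | 1 + 3 × 0.5 = 2.5 | 0.632 | 21.5% |
| 4 | 0.7 | 1 + 3 × 0.7 = 3.1 | 0.568 | 26.6% |
| 8 | 0.3 | 1 + 7 × 0.3 = 3.1 | 0.568 | 26.6% |
| 8 | 0.5 | 1 + 7 × 0.5 = 4.5 | 0.471 | 35.6% |
| 8 | 0.7 | 1 + 7 × 0.7 = 5.9 | 0.412 | 42.0% |

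**2. Within-patient contrast (change over time, group by time)**

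Here the patient's own level cancels. The true variance is (1 − ρ) times the naive one, so the naive standard error is too large. The actual type I error is 2[1 − Φ(1.96/√(1 − ρ))]:
- ρ = 0.3: 1.9%
- ρ = 0.5: 1.96/√0.5 = 2.77, giving 0.56%
- ρ = 0.7: 0.035%

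**3. Check by simulation**

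1,000 patients, 30% in one group, 8 visits, ρ = 0.5, no true group difference, 400 runs, linear model with visit effects. The group main effect was rejected in 32.5% of runs with naive standard errors and in 5.0% with patient-clustered standard errors. The Monte Carlo standard error of the first figure is √(0.325 × 0.675/400) = 2.3 percentage points, so 32.5% agrees with the 35.6% from the formula.

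**The case against.** The strongest reply is that the article nowhere says the scores are treated as independent. The paragraph stands under a heading about longitudinal data, and its last sentence binds every secondary model, including this one, to account for between-individual variability. For repeated scores that most naturally means a patient-level term. On this reading the label is loose shorthand for a generalized linear model extended with random effects or a working correlation. Clustered standard errors, or a separate model at each visit, would also be valid under the same label. The covariance structure is in any case a detail commonly left to a statistical analysis plan, which is not shown.

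Much of this stands. A reader might infer that the standard errors are too small and that the VS versus MCS comparison of quality of life will be declared significant too often. The document does not support that:
- The closing sentence shows an intention to handle clustering, so naive pooling cannot be taken as the plan.
- Study objectives states that "primary comparisons will be conducted at the VS vs. MCS level" for recovery, mortality and cardiovascular events. Baseline state is the primary exposure, so a contrast on EQ-5D is plausible, but none is stated.
- The direction of error is not general. It reverses for change over time and for group by time.

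What the reply does not remove is the mismatch in the text. The closing sentence names no mechanism, and the phrase about within-individual correlation is attached to the functional scores only. The same closing sentence also covers the negative binomial model for rehospitalization, where an overdispersion parameter could be held to satisfy it without any clustering. The model class is also stated, not omitted, so the analysis plan would have to override the article and not merely complete it.

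**Conclusion.** The point holds as an inconsistency in a stated method. EQ-5D is collected repeatedly on the same schedule as the functional scores, yet it is assigned a model class that, taken as named, has no within-patient correlation structure and fits poorly with the paragraph's own commitment.

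The consequence is conditional. It needs all visits pooled in one unclustered model, and its size rests on an assumed, equal correlation of 0.3 to 0.7 with 4 to 8 scores per patient. Under those conditions the type I error is about 15% to 42% for between-patient contrasts, and about 0.6% at a correlation of 0.5 for within-patient contrasts. If clustering is handled, as the closing sentence suggests is intended, the error returns to its nominal level (5.0% in the simulation). One secondary outcome is affected; the primary analyses are not.

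**What to change.** In Secondary analyses and longitudinal data analysis, replace the model named for quality-of-life scores with linear or generalized linear mixed models, or GEE with robust variance, matching the functional-status clause in the same sentence. The closing commitment then agrees with the method named. The covariance structure and the choice of a main contrast visit can be left to the statistical analysis plan.

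The cost is one line of wording, with no new data and no change to the schedule. Compared with a literal fit of the model now named, intervals for between-patient contrasts would widen to their correct width and those for change over time would narrow.

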### Subgroup and interaction analyses

Prespecified subgroup analyses will be conducted based on clinical relevance and potential effect modification, including: age (< 50 years vs. ≥ 50 years), sex (male vs. female), injury type (traumatic vs. non-traumatic), and baseline level of consciousness (VS vs. MCS). Interaction terms (product terms between the exposure variable and subgroup variables) will be introduced into multivariable regression models to formally test the statistical significance of interactions, with a significance threshold of *p* < 0.10. Statistically significant interactions will be further examined through stratified subgroup analyses, with results displayed as forest plots showing HRs and 95% CIs for each subgroup. All subgroup analyses will be characterized as exploratory findings to prevent overinterpretation.

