### Study population

The target population comprises individuals currently diagnosed with pDoC—specifically VS or MCS (encompassing both MCS − and MCS+)—at the time of enrollment. Patients who have already achieved eMCS prior to enrollment are not eligible, as eMCS constitutes the primary consciousness recovery endpoint of this study. Patients with post-traumatic confusional state (PTCS), which represents a transitional state beyond eMCS in the TBI recovery trajectory, are likewise not eligible for enrollment. Both conditions are characterized by persistent alterations in consciousness following severe acquired brain injury: VS is defined by wakefulness without awareness, whereas MCS indicates the preservation of partial conscious awareness.

Inclusion criteria are as follows: (1) a confirmed diagnosis of DoC with a duration of at least 28 days, established according to the 2020 European Academy of Neurology (EAN) guidelines (6) and assessed using the validated Chinese version of the CRS-R (7), including vegetative state (VS) and minimally conscious state (MCS; encompassing both MCS − and MCS+); (2) age between 18 and 80 years; (3) provision of written informed consent by the participant (if possessing decision-making capacity) or by a legally authorized representative (LAR); and (4) availability of complete medical records documenting the etiology of the initial brain injury, injury severity, and relevant diagnostic investigations. Eligible etiologies include all forms of acquired brain injury that can lead to prolonged disorders of consciousness (pDoC), such as traumatic brain injury (including both closed and penetrating head injuries) and non-traumatic brain injury—including hypoxic-anoxic injury (e.g., due to cardiac arrest, respiratory failure, or near-drowning), cerebrovascular events (such as ischemic stroke, hemorrhagic stroke, and subarachnoid hemorrhage), and metabolic or toxic encephalopathies.

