#### Exposure variable

The primary exposure variable is the baseline level of consciousness (VS or MCS) at enrollment. All enrolled participants will receive standardized multimodal rehabilitation care in accordance with the Chinese Expert Consensus on the Diagnosis and Treatment of Prolonged Disorders of Consciousness (Standard of Care, SOC) (10), encompassing: (1) pharmacological arousal-promoting therapy (e.g., amantadine, donepezil, zolpidem); (2) multimodal sensory stimulation therapy (auditory, tactile, visual, and olfactory modalities); (3) physical therapy (including tilt-table training and passive mobilization); (4) occupational therapy; (5) speech-language therapy; (6) hyperbaric oxygen therapy (where indicated and available); and (7) neuromodulation techniques (e.g., median nerve electrical stimulation, repetitive transcranial magnetic stimulation, spinal cord stimulation), as well as evidence-based complication management (infections, spasticity, pressure injury). Treatment intensity for each modality will be quantified as total weekly contact time (minutes per week) and session frequency, recorded prospectively in the electronic data capture system at each assessment timepoint. All treatment variables will be incorporated as time-dependent covariates (operationalized as weekly contact time (min/week) per rehabilitation modality) in the analytical models to distinguish the natural disease course from treatment-mediated effects.

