#### Predictor variables and covariates

Primary prognostic predictor variables have been selected based on established clinical and biological plausibility for predicting consciousness recovery: (1) etiology of brain injury (TBI, hypoxic-ischaemic encephalopathy, cerebrovascular event, metabolic/toxic encephalopathy, other), given that neurobiological recovery trajectories differ substantially across aetiological subgroups; (2) injury severity at the acute phase (GCS score at hospital admission); (3) time from acute brain injury to study enrollment; (4) CRS-R subscale scores at baseline (auditory, visual, motor, oromotor/verbal, communication, and arousal subscales); and (5) neuroimaging characteristics (white matter integrity on DTI, functional connectivity on fMRI). Pre-injury lifestyle characteristics [smoking status, alcohol consumption, physical activity (assessed via caregiver proxy report using IPAQ) (11), and dietary habits] are retained as exploratory secondary covariates; their collection is hypothesis-generating and their role as determinants of post-injury recovery will be interpreted with appropriate caution given the reliance on caregiver proxy report.

Pre-specified adjustment covariates in all multivariable models include age, sex, educational level, and comorbidities (e.g., cardiovascular disease, diabetes mellitus, chronic kidney disease). It should be noted that injury severity (GCS at acute admission) and the interval from injury to enrollment are designated as primary prognostic predictor variables in this study (see above), rather than as confounders, given their established direct effects on consciousness recovery trajectories; they will therefore enter the analytical models as predictors of interest rather than as adjustment terms. Effect modifiers—including age stratum (< 50 years vs. ≥50 years), injury type (traumatic vs. non-traumatic), and baseline CRS-R score—will be formally evaluated through prespecified subgroup analyses and interaction testing.

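### Age effect modification is tested only with age cut at 50; if the effect changes gradually with age, this discards about 25–33% of the information in an exploratory test

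*Protocol article*

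**What the plan says.** Two sections of the protocol article set the form of the age modifier. Predictor variables and covariates lists the effect modifiers as "age stratum (< 50 years vs. ≥50 years), injury type (traumatic vs. non-traumatic), and baseline CRS-R score". Subgroup and interaction analyses repeats the cut: "age (< 50 years vs. ≥ 50 years), sex (male vs. female), injury type (traumatic vs. non-traumatic". The latter section also fixes the test: "Interaction terms (product terms between the exposure variable and subgroup variables) will be introduced into multivariable regression models", with a threshold of p < 0.10. The exposure is defined under Exposure variable: "The primary exposure variable is the baseline level of consciousness (VS or MCS) at enrollment".

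The two-level age variable is therefore the stated interaction test, and not just a way of displaying results. Study population gives the eligible range as "age between 18 and 80 years", and Data sources and measurements records age in years. Where age enters as a covariate (Primary analysis, Models 2 to 5) or as a candidate predictor (the prediction model), no cut is stated. No test of exposure by continuous age appears.

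The status of these analyses is explicit: "All subgroup analyses will be characterized as exploratory findings to prevent overinterpretation".

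**The concern.** A product term with a binary age stratum treats patients aged 18 and 49 as alike, and patients aged 49 and 51 as different. If the VS vs MCS effect on recovery drifts with age, much of the age variation that would reveal the drift lies inside the two strata, where this test cannot see it. A test of interaction needs far more events than a test of a main effect, so the cut costs power where there is little to spare. What is at stake is a missed gradual modification by age, in a cohort that aims to describe prognosis over a wide age range. Labelling the results exploratory guards against over-reading a positive finding, but it does not help against missing one.

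**Working it through.** **The plan's own figure.** The article gives no power for any interaction. Its nearest figure is the 544 events for the main comparison. Schoenfeld's formula with HR 1.3, two-sided alpha 0.05, 80% power and 30% exposed gives (1.960 + 0.842)² / [0.30 × 0.70 × (ln 1.3)²] = 543, so 544 is reproduced. The same variance form is used below.

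**Inputs from the article (Sample size calculation; Subgroup and interaction analyses).** N = 1,000; 5-year recovery 34%; loss 15%; exposed 30%; interaction alpha 0.10, taken as two-sided.

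**Assumptions.** Loss is spread evenly over the 5 years. Modification is linear in age on the log-hazard scale. The age distribution is either uniform on 18–80, or normal with mean 50 and SD 15 truncated to 18–80.

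**Events.** Recovery rate −ln(0.66)/5 = 0.0831 per year; loss rate −ln(0.85)/5 = 0.0325 per year. Expected events = 1,000 × 0.0831/0.1156 × (1 − e^(−5 × 0.1156)) ≈ 316.

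**Information kept by the cut.** This is the squared correlation r² between age and the indicator of age 50 or over.
- Uniform: the share aged 50 or over is 30/62 = 0.484, and r² = 3 × (32/62) × (30/62) = 0.749. About 25% is lost.
- Truncated normal: the share is 0.497, the group means are 60.8 and 38.9 years, and the SD after truncation is 13.4. So r² = 0.497 × 0.503 × (21.9/13.4)² ≈ 0.67, and about 33% is lost.

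**Power.** With the cut, SE of the log ratio of hazard ratios = 1/√[316 × 0.21 × q(1−q)] ≈ 0.246, where q is the share aged 50 or over. The signal is ln(ratio)/SE, and power = Φ(signal − 1.645). With continuous age, the signal is divided by √r².

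| Ratio of HRs between age groups | Cut at 50 | Continuous, uniform age | Continuous, bell-shaped age |
|---|---|---|---|
| 1.4 | Φ(1.370 − 1.645) = 39% | Φ(1.582 − 1.645) = 48% | Φ(1.672 − 1.645) = 51% |
| 1.5 | Φ(1.651 − 1.645) = 50% | Φ(1.907 − 1.645) = 60% | Φ(2.015 − 1.645) = 64% |
| 2.0 | 88% | 95% | 96% |

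**Sensitivity to the event count (ratio 1.5, cut against continuous).** 289 events: 47% against 57–61%. 340 events: 53% against 63–67%. 544 events: 70% against 80–84%. The gain is 10 to 14 percentage points throughout.

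**Sensitivity to the age distribution.** Truncated normal ages centred at 50 with SD 12 to 18 lose 31–35%. Centred at 60 with SD 15 the loss is 38%; centred at 65 with SD 12 it is 56%.

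**Simulation check.** Cox models were fitted to 1,000 simulated patients with about 340 events and linear modification. The efficiency of the cut relative to continuous age was 0.75–0.76 (uniform) and 0.66–0.69 (bell-shaped). At a ratio of 1.5, power was 54% against 68% and 52% against 66%. These were ordinary Cox fits without competing deaths.

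**When the assumption fails.** With a true step at 50 and a ratio of 2.0, the cut was the more efficient test, by a factor of 1.3 to 1.5. Power was 92% for the cut against 86% (uniform) or 82% (bell-shaped) for linear age.

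**The case against.** The strongest reply is that a prespecified two-level stratum is conventional and easy to read, and that it rules out choosing a cut after seeing the data. The analysis is declared exploratory, and nothing in these sections is contradictory or miscalculated. All of that stands, and it limits the weight of the point.

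The direction of the loss also depends on a shape that nobody knows: a step at 50 would make the cut the better test. That stands too, so the claim has to be conditional.

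The change does not make the test strong, either. Continuous age reaches only 60–64% power at a ratio of 1.5, while at 2.0 the cut already has 88%. The main limit is the number of events: 1,000 × 34% gives about 340 before loss, against the 544 required. That is a separate matter, which this change does not cure.

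A reader might infer two stronger points that the article does not support. The first is that the boundary at 50 is arbitrary because no reason is given for it. A condensed article may leave that reason to the full protocol or analysis plan, so its absence here shows nothing. The second is that p < 0.10 decides whether any stratified result is seen at all. The section commits to the prespecified subgroup analyses without condition; the threshold governs which interactions are examined further.

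What survives is that the article itself fixes the two-level form of the test, in two places, although age in years will be available.

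**Conclusion.** The point holds in a conditional form and is minor. If the VS vs MCS effect changes roughly linearly with age and ages are spread around 50, the planned test uses about 67–75% of the information that continuous age would give. That costs about 10 to 14 percentage points of power at a ratio of hazard ratios of 1.5, and about 9 to 12 points at 1.4 (316 events, 30% exposed, alpha 0.10). The age distribution is an assumption, because the article states only the range; a cohort centred well away from 50 would usually lose more.

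It would be wrong to read this as an unconditional loss, since a step at 50 reverses it. It would also be wrong to read it as a weakness in the primary comparison: the VS vs MCS estimate does not use the age strata.

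**What to change.** In Predictor variables and covariates and in Subgroup and interaction analyses, state that modification by age will be tested with the product of exposure and continuous age. Make the linear term per 10 years the test at the same p < 0.10, with a 3-knot restricted cubic spline as a check on shape. Keep the strata below 50 and 50 or over for display in the forest plot only.

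The cost is about one sentence. No new data are needed, and splines are already among the tools named under Primary analysis. Enrolment is planned from June 2026, so the change can be prespecified before outcomes are seen. There are two small downsides: the result needs a plot or estimates at a few chosen ages to be read easily, and some power is lost if the true effect is a step at 50.
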